**Aim:**

The aim of the project is to investigate whether daily intake of two plant extracts for a period of three months can improve reduced semen quality in men.

The causes of reduced semen quality may be many. It is the aim of this project to find a treatment, which can be used in cases where reduced semen quality is environment and coupled to oxidative stress.

**Background:**

Reduced semen quality is a big and recognized problem in many western countries, not the least in Denmark, where it is estimated that up to 40% of young men is affected to some extend (1). To this day the focus has been on symptomatic treatment with assisted reproduction. This method is relatively expensive from a social perspective and often causes considerable inconvenience for the female part. Therefore, a treatment, which can improve the semen quality and decrease the need for assisted reproduction, is in high demand.

Plant ingredients against reduced semen quality

The project is based on a thorough and systematic search in the scientific literature with the aim to encircle plant extracts with a positive effect on the semen quality in human and/or animals. The criteria for choosing extracts for testing in a clinical trial was:

1. The plant extract should have shown a positive effect on semen quality in human and/or animals.
2. The plant extract should be approved as article of food in Denmark or the EU.
3. The plant extract must not have shown serious side effects in previous trials.

Based on these criteria two plant extracts was encircled:

Greater galangal (*Alpinia galanga* (Willd.) L.)

Pomegranate (*Punica granatum* L.)

Existing literature on these two plants was assessed with focus on effect on semen quality and other physiological properties, chemical substances, and safety.

*The effect of greater galangal on semen quality*

The effect of greater galangal on semen quality has been addressed in experiments with mice (2), where intake of the ethanolic extract for three months resulted in significantly improved motility of spermatozoa (P < 0.01) and an increased number of spermatozoa (P < 0.05). Additionally, an experiment with rats showed that intake of greater galangal increased the level of serum testosterone (3). A sufficiently high serum testosterone level is crucial for normal sperm production. The active component of greater galangal is not known, but it is possibly one or more phenylpropanoids, a group of components characteristic for greater galangal (4). The present studies do not indicate any safety risk with the intake of greater galangal (2, 5).

*The effect of pomegranate on semen quality*

The effect of pomegranate on semen quality has been addressed in experiments with rats (6), where intake of juice for seven weeks resulted in significantly increased sperm concentration (P < 0.01), improved motility (P < 0.05), and a decreased frequency of abnormal sperm (P < 0.05).

A different experiment on rats showed that a single component from pomegranate, ellagic acid, was able to counteract the negative effect on semen quality caused by cisplatin (7). Also in this study the oxidative balance in semen and serum was significantly improved.

In addition, juice from pomegranate has been shown to improve the oxidative balance in human serum (8, 9), which may be due to a high level of antioxidants, particularly ellagitannins and ellagic acid (10). One of the animal experiments indeed suggests that ellagitannins and ellagic acid play a central role in the improvement of the semen quality (7). The present studies do not indicate any safety risk with the intake of pomegranate (8, 11, 12), only risks of allergic reactions, which may appear following intake of many other fruits (13) cannot be excluded.

*In summary*

We have increased to ingredients, greater galangal and pomegranate, which both may improve semen quality, and which both are approved as food in the EU.

Causes of reduced semen quality

No unambiguous explanation exists to why reduced semen quality has become an increasing problem in Denmark and other western countries (14, 15). Among other factors, smoking during pregnancy (16), hormone disrupting components (17), obesity (18), and oxidative stress (19) have been linked to reduced semen quality.

In this project it is hypothesized that oxidative stress plays a substantial role in the development of reduced semen quality (20). Oxidative stress may appear due to environmental influences or health conditions and can be identified by a high level of reactive oxygen species (21). High levels of reactive oxygen species may damage the sperm membrane and DNA, and as a result the sperm will become defect (22). Oxidative stress may be neutralized by antioxidants, which inhibit the formation of reactive oxygen species (19).

Greater galangal and pomegranate both contain a high level of various antioxidants (23, 10). It is therefore reasonable to assume that these two ingredients have the ability to neutralize oxidative stress and as a result improve semen quality.

**Methods:**

**Design:** The study will be carried out as a randomized, double-blinded, placebo-controlled trial with two arms of equal size.

**Recruitment:** Participants will be reruited via the sperm bank Nordic Cryobank. Participants must be at least 18 years of age. Potential participants will be given written information and a declaration of consent at the sperm bank, and concomitantly they will be offered an elaborating conversation with [name]. If the man – after time to think it over – decides to participate, oral and written consent is obtained. On a regular basis approximately 1-2 men per week are declined as sperm donors in Nordic Cryobank due to reduced semen quality. Men who do not fulfil the donor criteria with respect to sperm count are offered a second semen analysis, and in the case the second sample remains at an equal standard the man is offered participation. Two analysed ejaculates prior to the treatment are required.

**The trial:**

When a potential participant has been given oral and written information about the trial and given his written consent, biostatistician professor [name] will randomize him to get tablet containing either extracts of pomegranate and greater galangal or placebo tablets. The participant will concomitantly receive a questionnaire, which he is encouraged to fill out and return just prior to the cure. At the end of the three months of daily intake of tablets the participants will deliver two ejaculates with 4-10 days of interval. The treatment will be continued until the last ejaculate is delivered.

In addition to the start- and end-ejaculates, the participants are asked to deliver one ejaculate 4-8 days after treatment start to provide information on whether a possible effect can be measured after a short treatment time.

The ejaculates can be collected in Aarhus (where many of the potential participants expectedly live) but will be examined in the laboratory of Scientific Unit of Reproduction Biology, Horsens Regional Hospital. With the delivery of the last ejaculate the participant will receive kr. 1500 corresponding to kr. 300 per ejaculate. If a participant leaves the trial before the three months have passed, he will receive kr. 300 per delivered ejaculate. An experienced laboratory technician will together with [name] manage: the recruitment of participants, informing the participants about the trial, handling the hand-over of tablets, and administrating and coordinating the hand-in and analysis of ejaculates. The fact that the practical work is all handled by one experienced laboratory technician ensures that all analyses are carried out as similarly as possible.

The active treatment consists of a daily intake of 2x 1 gram of dried ethanolic extract of greater galangal and dried pomegranate corresponding to 500 mL of fresh pomegranate juice. The extracts are standardized from HPLC-measures of marker components. Both extracts are given as tablets. The placebo treatment holds daily intake of a corresponding number of tablets containing inactive components.

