**Statistical analyses:**

Changes in the total number of spermatozoa will be compared between the two groups, which are receiving active treatment and placebo treatment, respectively, using relevant statistical analyses.

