**Number of participants / power estimation:**

With a significance level of 5%, a statistical power of 80%, and a confidence interval of 2 million motile sperm, at least 18 participants should be included in each group ([name], Institute for Biostatistics, AU). However, we request permission to include 100 participants, thus 50 participants per arm.

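### Men are randomised on consent with no described use of the two required baseline sperm counts; stratifying and adjusting on them would cheaply protect precision, mainly near the minimum of 18 per arm

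*Protocol*

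**What the plan says.** The protocol's section *The trial* describes allocation in one sentence. After information and consent ("given his written consent, biostatistician professor"), the biostatistician randomises the man to extract or placebo tablets. The sentence gives the trigger and the role responsible. It names no strata, blocks or minimisation, and neither does any other section.

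*Methods* describes a "placebo-controlled trial with two arms of equal size". Under recruitment it adds: "Two analysed ejaculates prior to the treatment are required". Participation is offered only after a second semen analysis has confirmed the low result.

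*Inclusion criteria* admits otherwise healthy men with semen quality below donor level. *Exclusion criteria* removes azoospermia but sets no other lower limit on count.

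*Statistical analyses* says: "Changes in the total number of spermatozoa will be compared between the two groups". The method is left open, and baseline adjustment is neither stated nor ruled out.

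*Number of participants / power estimation* says "at least 18 participants should be included in each group", then asks permission for 100 men, "thus 50 participants per arm".

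**The concern.** A man's sperm count before treatment is likely to be a strong predictor of his count at the end, and the protocol already requires it to be measured twice. Allocation is settled man by man at enrolment. If the counts play no part then, a later analysis plan can adjust for an imbalance but cannot prevent it.

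In a comparison of changes, the arm that happens to start higher tends to fall and the arm that starts lower tends to rise. A chance gap at baseline therefore moves the estimated treatment difference, in either direction, unless baseline is in the model. The smaller the trial, the larger the gap that chance can produce, and the only size the protocol justifies by calculation is 18 per group.

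**Working it through.** **The plan's own figure.** The protocol reads: "With a significance level of 5%, a statistical power of 80%, and a confidence interval of 2 million motile sperm", giving 18 per group. No SD is stated, so 18 can only be solved backwards. Taking 2 million as the difference to detect, two-sided, SD = 2 / [(1.960 + 0.842) × √(2/18)] = 2.14 million. Taking it as a 95% confidence-interval half-width instead, SD = 2 / [1.96 × √(2/18)] = 3.06 million. Neither can be confirmed. Below, 18 and 50 per arm are used only as the stated minimum and requested sizes.

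**Assumptions (not in the protocol).** The log of the mean baseline total count has SD 1.0 between men (range 0.7 to 1.2), with equal SD at the end. The correlation ρ between baseline and end is 0.5 to 0.7. Arms are equal in size.

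**Chance of a 1.5-fold baseline gap.** The standard error of the difference in log means is SD × √(2/n), and ln 1.5 = 0.405. The chance is P(|Z| > 0.405 / SE).

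| n per arm | SD | SE | 0.405 / SE | Chance, no strata | Chance, two median strata (simulated) |
|---|---|---|---|---|---|
| 18 | 0.7 | 0.233 | 1.74 | 8% | 1% |
| 18 | 1.0 | 0.333 | 1.22 | 22% | 5% |
| 18 | 1.2 | 0.400 | 1.01 | 31% | 11% |
| 50 | 0.7 | 0.140 | 2.90 | 0.4% | 0% |
| 50 | 1.0 | 0.200 | 2.03 | 4% | 0.1% |
| 50 | 1.2 | 0.240 | 1.69 | 9% | 0.7% |

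Simulation without strata (6,000 trials per setting) gave 8, 23 and 32% at 18 per arm, in line with the closed form.

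**Effect of such a gap on a change score without baseline in the model.** With no treatment effect, the expected difference in change is −(1 − ρ) × gap. For a 1.5-fold gap its size is 0.5 × 0.405 = 0.20 log units at ρ = 0.5 and 0.3 × 0.405 = 0.12 at ρ = 0.7, or 22% and 13% in count.

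**Validity.** Over all randomisations this averages out. At ρ = 0.6, the simulated type I error of an unadjusted change-score t-test, with equal arms and no strata, was 5.2% at 18 per arm and 4.6% at 50.

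**Precision.** In units of the between-man variance:

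- The change score has variance 2(1 − ρ). With baseline as covariate the residual variance is 1 − ρ². The ratio is (1 + ρ)/2, which is 0.75 at ρ = 0.5 and 0.85 at ρ = 0.7, a saving of 15 to 25%.
- Two median strata reduce the simulated SE of the baseline gap at 18 per arm from 0.332 to 0.202 SD, so its variance is multiplied by (0.202/0.332)² = 0.37. The variance ratio for the change comparison is then [(1 + ρ) + 0.37(1 − ρ)]/2: 0.84 at ρ = 0.5 and 0.91 at ρ = 0.7. Simulation with blocks of 4 gave 0.84 to 0.93, a saving of 7 to 16%.
- Once baseline is in the model, chance imbalance inflates the variance by only about 1/(2n − 4), which is 1/32 = 3% at 18 per arm. Stratifying can recover at most that.

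**Strata need to be carried into the analysis.** With stratified allocation but an unadjusted t-test on changes, the simulated type I error at ρ = 0.6 fell to 3.6% (18 per arm) and 3.3% (50 per arm). The test is then conservative and part of the gain is lost.

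**The case against.** A reader might infer that the change comparison is unadjusted. The protocol does not say so: it leaves the method open, a change comparison can carry baseline as a covariate, and the model may be set out in an analysis plan that is not shown. The 13 to 22% shift above arises only if baseline is left out.

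A reader might also infer that men are allocated by the toss of a coin. Under that scheme, exactly 18:18 would occur in 13% of trials of 36 men and exactly 50:50 in 8% of trials of 100. But no such scheme is described, and the commitment to "two arms of equal size" points, if anything, to some form of restriction. Those figures do not count against this protocol. Non-use of the counts is likewise read from silence, and block details are often kept out of a protocol on purpose.

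The requested size is 50 per arm, where a 1.5-fold gap is uncommon and a gap above 0.5 SD has a chance of about 1% (13% at 18 per arm). The SD and correlation are assumed. Donor level is not given, so the true spread of baseline counts is unknown. Chance imbalance is also already reflected in the standard error.

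All of this stands, and it limits the point to precision and conditional balance. What it does not answer is timing: allocation happens at enrolment, so an analysis plan cannot introduce stratification afterwards. Nor does the protocol settle whether the counts are in hand at allocation. The payment of kr. 1500 at kr. 300 each covers five ejaculates (two start, one early, two end), but the text does not say whether the two start samples are those from the sperm bank or are collected after consent. On the second reading, randomising on consent could precede the baseline counts.

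**Conclusion.** The point holds as a cheap improvement to the design, not as an error that undermines the trial. The protocol ties randomisation to consent, describes no use in allocation of the two baseline counts it requires, and names a comparison of changes without stating baseline adjustment. The test remains valid on average.

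The exposure is mainly at or near 18 per arm: about a 22% chance of a 1.5-fold baseline gap if the log SD is 1.0, and about 8 to 32% across SD 0.7 to 1.2. At 50 per arm and SD 1.0 it is about 4%.

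Baseline adjustment brings the larger precision gain. Stratification is worth about 7 to 16% of variance if the comparison is otherwise unadjusted, and a few per cent at most if baseline is modelled. These figures depend on the assumed SD and on a correlation of 0.5 to 0.7.

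**What to change.** In *The trial*, state that a man is randomised after written consent and after both pre-treatment ejaculates have been analysed. Allocate 1:1 in permuted blocks of varying size within two strata of the mean total sperm number of those two ejaculates. Fix the cut before recruitment starts, for example near the median of men the sperm bank has declined. The biostatistician prepares the two lists in advance. Blocking also keeps the arms close to equal wherever recruitment ends between 36 and 100 men.

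In *Statistical analyses*, state that end counts or changes are compared with the mean baseline count, suitably transformed, as a covariate, together with the stratum. On the same scale and with the same covariates, end count and change give the same treatment estimate.

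The cost is a few sentences of protocol text and two lists instead of one. The one drawback is that the biostatistician must receive both counts before allocating. No extra men, samples or staff are needed.

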**Semen analysis:**

The effect of the treatment is evaluated from measurements of the following classic semen parameters: concentration (sperm/mL), motility, and morphology. The measurements will be performed according to the WHO guidelines (24).

The total number of motile sperm (ejaculate volume x concentration of sperm x per cent of motile sperm) is a combined measure of semen quality. All ejaculates will be discarded immediately after analysis.

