**Preparation and dosage of plant components:**

The participants are receiving greater galangal as a dried capsulated ethanolic extract, because the before mentioned animal experiments was based on such extract (2, 3). Pomegranate will be prepared as dried and capsulated juice.

The daily dose of galangal extract will be set at 2 g. This is in fact a lower dose than that used in the experiment with mice (2) (which would give a dose corresponding to 8 g for a man of 80 kg). The lower dose is chosen in order to minimize potential side effects such as gastric irritation, and because the effective dose of the related drogue ginger often is kept at this level (14).

The daily dose of dried pomegranate juice will be set at an amount corresponding to 500 mL of fresh juice. This amount is higher than that used in the before mentioned rat experiment (6) and is thus expected to be sufficient when thriving to reach a measurable effect.

We request that information about the identity, preparation, and dosage of the plant extracts will be kept confidential.

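### The protocol names gastric irritation and allergic reactions as possible product effects but specifies no recording of side effects, illness or missed tablets during treatment

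*Protocol*

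**What the plan says.** The only self-report instrument is described in the Protocol under The trial. Each man is to "receive a questionnaire, which he is encouraged to fill out and return just prior to the cure". Its content is not described, and it is not repeated.

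Samples are scheduled as follows:

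- **Before treatment** (Methods, Recruitment): "Two analysed ejaculates prior to the treatment are required".
- **Early** (The trial): "the participants are asked to deliver one ejaculate 4-8 days after treatment start". The stated purpose is to see whether an effect is measurable after a short time.
- **End** (The trial): "At the end of the three months of daily intake of tablets the participants will deliver two ejaculates with 4-10 days of interval". The same section adds: "The treatment will be continued until the last ejaculate is delivered".

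The outcome is defined on semen alone (Semen analysis): "The effect of the treatment is evaluated from measurements of the following classic semen parameters: concentration (sperm/mL), motility, and morphology".

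Two product effects are acknowledged. On the galangal dose, Preparation and dosage of plant components says: "The lower dose is chosen in order to minimize potential side effects such as gastric irritation". On pomegranate, the Background says that allergic reactions cannot be ruled out. The section Risks and precautions addresses only the semen measurements.

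**The concern.** The protocol expects that the products might cause symptoms, and gives gastric irritation as one reason for its choice of galangal dose. It then plans no data that would show whether such symptoms occurred. This cannot be left to a statistical analysis plan, because that plan can tabulate only what was collected.

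Two things are at stake:

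- **Tolerability.** The product is tried in men who must be otherwise healthy (Inclusion criteria). A placebo-controlled side-effect comparison is something this trial could supply at little cost, and the plan does not provide for it.
- **Explanation of the semen result.** If the active tablets caused gastric trouble, men in that arm might skip tablets or leave. The trial section foresees early leavers and sets their payment, but it plans no record of the reason. Symptoms of genital infection exclude a man at entry (Exclusion criteria), yet no question about them is planned when the outcome samples are given three months later.

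**Working it through.** The protocol gives no tolerability figure to reproduce, and its minimum of 18 men per group does not bear on this point. The check is a reading of the sections side by side, plus visit arithmetic.

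**1. Number of sample visits.** Inputs from The trial: kr. 1500 in total and kr. 300 per ejaculate. 1500 / 300 = 5. The schedule gives 2 before treatment + 1 early + 2 at the end = 5. The payment therefore points to no further sample visit, and three of the five visits fall on treatment.

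**2. Length of treatment.** Take three months as 90 days (assumption). If the first end sample falls on day 90, the second follows 4 to 10 days later, and treatment runs to that sample: 90 + 4 = 94 to 90 + 10 = 100 days.

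**3. Interval a form would have to cover by recall.** From the early sample (day 4 to 8) to the first end sample: 90 − 8 = 82 to 90 − 4 = 86 days. With three months taken as up to 92 days, the upper limit is 92 − 4 = 88 days. Tablet hand-over dates are not stated, so a contact in this interval is possible but not described.

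**4. What is acknowledged against what is recorded.**

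| Item | Where acknowledged | On-treatment recording specified |
|---|---|---|
| Gastric irritation | Preparation and dosage | None |
| Allergic reaction | Background | None |
| Genital infection symptoms | Exclusion criteria (entry only) | None |
| Leaving early | The trial (payment only) | No reason recorded |
| Missed tablets | Not mentioned | None |

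**5. What a record could show with 50 men per arm.**

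- Chance of seeing at least one case of an effect with a true rate of 6% (illustrative): 1 − 0.94^50 = 0.955.
- If no case were seen in 50 men who had been asked, the one-sided 95% upper limit for the rate is 1 − 0.05^(1/50) = 0.058, about 6%.
- Comparison with placebo is weaker. A 6% rate gives 3 expected cases. For 3/50 against 0/50, two-sided Fisher p = 2 × C(50,3) / C(100,3) = 2 × 19,600 / 161,700 = 0.24.
- Against 0/50, 5 cases give 2 × 2,118,760 / 75,287,520 = 0.056, and 6 cases give 2 × 15,890,700 / 1,192,052,400 = 0.027. About 6/50 (12%) is therefore the smallest count that reaches the 5% level.

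A record would thus describe side effects usefully and bound their frequency, but it would show a difference from placebo only for fairly common effects.

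**The case against.** The strongest case on the other side has five parts.

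**Silence is not prohibition.** A reader might infer that side effects would never be recorded and that the chance of seeing one is zero. The protocol does not support that. One technician meets the men at three on-treatment visits and hands over tablets on unstated dates, and nothing stops a man from reporting a symptom. What stands is narrower: no recording is specified, and informal notes do not give a systematic comparison by arm.

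**The efficacy comparison survives.** A reader might also infer that a poor end sample could not be interpreted. The Methods make the trial randomised, double-blind and placebo-controlled, Statistical analyses compares changes between arms, and each man gives two samples before treatment and two at the end. Unrelated illness should balance on average and mainly adds noise. This objection stands in full for the group comparison. It does not cover illness or missed tablets caused by the product, which need not balance.

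**The long interval between visits is not itself the defect.** It is tempting to put the 82 to 88 days without a described contact at the centre. The missing record can be largely repaired at the visits already planned, so the interval counts as a source of recall error.

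**Low expected risk and no tolerability aim.** The Background describes both plants as approved foods, with no safety risk indicated apart from possible allergy, and the protocol states no tolerability objective. This limits the severity: a safety record is lost, not a named outcome. It does not remove the gap, since the protocol itself names two effects.

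**A symptom form could threaten blinding.** Gastric or allergic symptoms may hint at the active arm, and the same technician runs the visits and the analyses. This stands and shapes the fix.

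**Conclusion.** The point holds in limited form. Followed as written, the protocol yields no systematic data on side effects, intercurrent illness or missed tablets during about 94 to 100 days of treatment, although it names two product effects as possible. Tolerability could not be compared with placebo, and a product-related illness or missed tablets could not be separated from a direct effect on sperm. The randomised comparison of semen change remains valid.

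The conclusion rests on reading three months as about 90 days, and on the absence of any other described contact or form. The gain from a record is moderate: with 50 men per arm it would very probably reveal an effect occurring in 6% of men, but would separate the arms only at roughly 12% against none. The change should be made because the information cannot be reliably reconstructed afterwards and is cheap to obtain. It is not a condition for the semen analysis to stand.

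**What to change.** Amend The trial so that each man completes one short standard form at the three existing on-treatment visits (the day 4 to 8 sample and both end samples), and at withdrawal if he leaves early. It should cover gastric symptoms, allergic symptoms, fever, genital infection symptoms, medicines taken, and tablets missed since the last visit. At withdrawal it should also ask the reason.

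Have the form returned sealed, so that the technician who examines the samples does not see it. Tabulate the answers by arm. Name a role to receive reports between visits, and extend Risks and precautions to mention the two effects acknowledged elsewhere. Any repeat of the comparison without samples given during an infection can be left to the statistical analysis plan.

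The cost is a page of paper and a few minutes per man at visits already planned, one extra table, and the handling needed to keep the forms away from the person analysing the samples. Recall over 82 to 88 days will be imperfect, so mild or brief symptoms in the middle of treatment will be under-reported. With blinding intact, that should affect both arms alike.
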